#### Secondary outcome measures—patients

##### Self-management skills

The 40-item Dutch Version of the heiQ [39] consists of eight domains, namely skills and technique acquisition which is the primary outcome (composite reliability 0.82), health directed activity (composite reliability 0.82), positive and active engagement in life (composite reliability 0.81), emotional distress (composite reliability 0.89), self-monitoring and insight (composite reliability 0.67), constructive attitudes and approaches (composite reliability 0.86), social integration and support (composite reliability 0.85), and health service navigation (composite reliability 0.85) [39]. Response options are based on a 4-point Likert scale: ‘Strongly disagree’ (1), ‘Disagree’ (2), ‘Agree’ (3), ‘Strongly agree’ (4). Interpretation of the heiQ is through mean scores on each domain, with subscale scores ranging between 1 and 4. Higher values on the domain indicate higher levels of self-management, with the exception of the scale ‘Emotional distress’, for which the interpretation is reversed.

##### Self-regulation in the context of transplantation

Currently available self-report measures of self-management among patients do not address all elements incorporated into the intervention and are generic. Therefore, a new self-report instrument based on the self-regulation theory [34] was developed tailored for the use in transplant recipients. An expert group and a group of kidney transplant patients assessed the item pool on relevance via the Content Validity Index [40] (expert group) and the Three-Step Test-Interview [41] (patients). The current item pool was scored as relevant, comprehensive and feasible, and therefore will be used in this study. The instrument consists of 47 items and assesses eight domains: awareness, attitude, self-efficacy, motivation, social support, skills, social comparison, and goal affect. With confirmatory factor analysis, we will establish the internal structure of this scale. Response options are ‘Strongly disagree’ (1), ‘Disagree’ (2), ‘Neither agree nor disagree’ (3), ‘Agree’ (4), ‘Strongly agree’ (5). Mean scores are calculated per domain. A higher score on the scale indicates a higher level of self-regulation skills in the context of a transplantation. We are in the process of testing the measurement properties which will be reported separately.

##### Quality of life

To assess quality of life (QoL), the 26-items World Health Organization Quality of Life – Brief Version (WHOQoL-BREF) [42] will be used. This instrument consists of five domains: physical health (Cronbach’s alpha = 0.80), psychological (Cronbach’s *α* = 0.74), social relationship (*α* = 0.66), environment (*α* = 0.73), and overall QoL and general health. Mean scores are calculated per domain as well as for the overall QoL. A higher score on the scale(s) indicates a higher level of QoL.

##### Medication adherence

Medication adherence will be assessed with the Basel Assessment of Adherence to Immunosuppressive Medication Scale (BAASIS©) [43]. The BAASIS is divided into two parts. The first part consists of four questions, with the answer options ‘Yes’ (1) and ‘No’ (0). If ‘Yes’, to any of these items, the second part needs to be answered; the patient will be asked to answer how often they are non-adherent: ‘Never’ (1), ‘Once a month’ (2), ‘Every 2 weeks’ (3), ‘Every week’ (4), ‘More than once a week’ (5), ‘Every day’ (6). When one of the items of the first part is answered with ‘Yes’, the patient is considered non-adherent.

#### Secondary outcome measures—nurse practitioners

##### Self-management support skills

The self-management support skills of the NPs before and after the experimental period will be evaluated using the Self-Efficacy and Performance in Self-Management Support (SEPSS-36) instrument [44]. The aim of the instrument is to assess self-efficacy and performance in self-management support. The SEPSS consists of 36 items, which are structured according to the Five-A’s model [45]. The items are divided into six subscales, namely assess (self-efficacy Cronbach’s *α* = 0.85; performance *α* = 0.84) , advise (self-efficacy *α* = 0.82; performance *α* = 0.75), agree (self-efficacy *α* = 0.89; performance *α* = 0.88), assist (self-efficacy *α* = 0.87; performance *α* = 0.85), arrange (self-efficacy *α* = 0.84; performance *α* = 0.82), and overall competencies (self-efficacy *α* = 0.83; performance *α* = 0.81). The response options for the items assessing self-efficacy are ‘Not at all’ (0), ‘Not sufficient’ (1), ‘More or less’ (2), ‘Sufficient’ (3), ‘Good’ (4). The items that assess performance can be scored with the following response options ‘Never’ (0), ‘Rarely’ (1), ‘Occasionally’ (2), ‘Frequently’ (3), ‘Always’ (4). Interpretation of the SEPSS is through the mean score on the subscale, ranging from 0 to 4. The scale total, self-efficacy and performance, will be calculated by summing the subscale scores, with a range from 0 to 24. A higher score indicates a higher level of self-efficacy or performance in self-management support.

##### Need-supportive counselling

The self-management support skills of the participating NPs will be objectively evaluated in the control and experimental period, via video observations using the Coding and Observing Need-Supportive Counselling in Chronic Care Encounters (COUNSEL-CCE) [46]. The patients and NPs who will be filmed, will be asked to give consent. Each NP will be filmed at least once in each period. The patients who are filmed will be a convenience sub-sample among participants. The aim of the instrument is to observe need-supportive and need-thwarting counselling in chronic care encounters. The COUNSEL-CCE (46) consists of 44 items divided into nine scales of behavioural approaches, namely participative (Cronbach’s *α* = .69), attuning (*α* = .88), guiding (*α* = .72), clarifying (*α* = .54), demanding (*α* = .78), domineering (*α* = .75), abandoning (*α* = .33), awaiting (*α* = .33), and relatedness supportive reciprocity (*α* = .81). Response options are based on a 4-point Likert scale range from ‘never observed’ (0) to ‘all the time observed’ (4). Procedure for the observation is: observation of the interaction between professional and patient during a 5-min interval, coding of the observed interval, observing the same interval for the second time, and coding any aspects missed. Before scoring the observations, the researchers will be trained in use of the manual, which is provided by the developers of the instrument. For each scale, a mean score will be calculated.

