We will assess the differences on the primary and secondary outcomes between patients in the control period and versus the experimental period at both T1 and T2 on the outcomes (between-groups comparison). We will also assess the differences on the outcomes between T0–T1 and T0–T2 within the control period and within the experimental period (within-groups comparison). The secondary outcome measure *medication adherence*, which is a dichotomous variable, will be analysed with a generalized estimating equations logistic regression. If the effect of the intervention is found to differ according to organ type then separate explorative multivariate analyses will be conducted to assess the effect per organ.

Among NPs, in an initial univariate analysis, we will compare self-management support skills, using all scales of the SEPSS-36, before and after the experimental period (T0-prior to training and T1-at the end of the implementation period). For non-normally distributed data, we will use the Wilcoxon signed-rank test and the paired samples *t* test in case of normally distributed data.

The video recordings of the NPs will be assessed in blocks of 5 minutes each. Of every recording, a 5-minute clip will be randomly assigned to be observed by two researchers independently. The clips from the control period will be compared with the clips of the experimental period on the needs-thwarting and needs-supporting subscales and tested using the Wilcoxon-signed rank test for non-normally distributed data and the paired samples t-test in case of normally distributed data.

The interviews and qualitative questions in the questionnaire, which will be used to qualitatively evaluate the intervention and the nurse-led care, will be transcribed by at least two researchers independently and analysed thematically [55] using NVivo.

To examine if contamination occurred, we will compare the primary outcome (Skills and Technique Acquisition - heiQ) among control period patients in the contamination phase versus those in the control period not in the contamination phase at T1 and T2. This will be done using an independent samples *t* test. If there is a significant difference, we will control for contamination in the main multivariate analysis.

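### Filming a convenience choice of patients, who differ between periods, lets the COUNSEL-CCE comparison partly reflect who was filmed; two minor measurement points need tidying

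*Protocol article*

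**What the plan says.** The section on need-supportive counselling says that NP skills "will be objectively evaluated in the control and experimental period, via video observations". On whom and how often to film it says "The patients who are filmed will be a convenience sub-sample among participants" and "Each NP will be filmed at least once in each period". It gives no rule for choosing the filmed patients and does not say who chooses them. The coding procedure observes the interaction between professional and patient in five-minute intervals.

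The instrument "consists of 44 items divided into nine scales of behavioural approaches". The alphas listed include "attuning (*α* = .88), guiding (*α* = .72), clarifying (*α* = .54" and "abandoning (*α* = .33), awaiting (*α* = .33"; the other scales run from .69 to .81. The response format is given as: "Response options are based on a 4-point Likert scale range from ‘never observed’ (0) to ‘all the time observed’ (4".

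Under Data analysis, one five-minute clip per recording is assigned at random to two researchers who work independently. Control-period clips are then "compared with the clips of the experimental period on the needs-thwarting and needs-supporting subscales", by Wilcoxon signed-rank or paired t test.

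Study design and randomization says that the trial is unblinded, that NPs cannot be blinded, and that no patient belongs to both periods.

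**The concern.** How supportively a nurse counsels in one consultation depends partly on the patient in the room. If the filmed patients are whoever is convenient, the mix can change between periods for reasons unrelated to the nurse's skill. With one recording per period, a single patient can determine an NP's score for that period. Nothing in the text keeps the choice the same before and after training, and the period is known to the NP.

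At stake is aim 3, whether training and delivering the intervention changes NP skills. Table 2 in the Appendix lists three NP measures: SEPSS-36, a semi-structured interview and COUNSEL-CCE. The first two are the nurse's own account. The recordings are therefore the only check under this aim that is not self-report, and the text presents them as objective. A difference produced by selection would be read as a gain in skill.

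**Working it through.** **1. Selection of filmed patients.** The plan has no figure to reproduce here, so I set its statements against a simple model. Write the clip score of NP *i* in period *t* as

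score = a_i + s_t + p_it + e_it

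where a_i is the NP's stable level, s_t is skill in the period, p_it is the contribution of the filmed patient or patients, and e_it is clip and coding error. The paired difference, experimental (E) minus control (C), is

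D_i = (s_E − s_C) + (p_iE − p_iC) + (e_iE − e_iC)

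and its mean over NPs estimates the skill change plus (mean p_E − mean p_C).

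What each stated safeguard removes:
- Filming every NP in both periods, with paired tests: removes a_i. It does not remove the patient term, because the patients differ between periods.
- Random five-minute clip: guards against choosing a favourable part of a recording (part of e). It acts after the patient has been chosen.
- Two independent trained coders who view each interval twice: reduces coding error (part of e). This also comes after the patient has been chosen.
- More than one recording per NP per period: reduces random variation in p, but leaves any systematic difference between mean p_E and mean p_C.

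Only a selection rule that is the same in both periods acts on mean p_E − mean p_C, and the stated method is convenience. The documents give neither the share of score variance due to patients nor the number of NPs, so this term cannot be sized.

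**2. Low-alpha scales.** The nine alphas are participative .69, attuning .88, guiding .72, clarifying .54, demanding .78, domineering .75, abandoning .33, awaiting .33 and relatedness supportive reciprocity .81. Six of nine are .69 or higher, one is .54 and two are .33.

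Taking alpha as the reliability of the scale score (an assumption), observed standardised effect = true effect × √alpha. For an assumed true shift of 0.50 SD:
- alpha .88: √.88 = 0.938; 0.50 × 0.938 = 0.47
- alpha .54: √.54 = 0.735; 0.50 × 0.735 = 0.37
- alpha .33: √.33 = 0.574; 0.50 × 0.574 = 0.29

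On the same reading the error share of variance is 1 − .33 = 67% for abandoning and awaiting, and 1 − .54 = 46% for clarifying. Attenuation shrinks a true difference; it does not create one.

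**3. Response format.** Integer codes from 0 to 4 are 0, 1, 2, 3, 4: five categories. Four categories would need 0 to 3 or 1 to 4. The article's own SEPSS-36 description lists five options for codes 0 to 4. The text does not show which COUNSEL-CCE format is meant.

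**The case against.** The best defence is that the design already limits bias. Every NP serves as their own control, the clip is random, and trained coders work independently from the developers' manual. One recording is a minimum, not the plan. That an NP would film an easier patient after training is conjecture, since the article does not say who chooses. NP awareness of the period is unavoidable and disclosed. The outcome is secondary in a trial about patients.

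Most of this stands and lowers the severity. It does not answer the point, because none of these safeguards acts on the choice of patient. Nor is this a detail merely left to a fuller document: the article states the method, and the method is convenience. No deliberate selection is needed; a change in who is easy to film would be enough.

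Three stronger readings are tempting, and the documents do not support them.
- A reader might infer that the whole endpoint is uninterpretable. Six of nine scales have alpha of .69 or more, and low alpha weakens null results without producing false differences. Alpha is also internal consistency, not agreement between raters.
- A reader might infer that three times as many NPs are needed at alpha .33, from 1/.33 = 3.0. That is not derived for the planned paired test, where the reliability of the change score governs. This depends on the within-NP correlation between periods, which is not given.
- A reader might infer that a finding of no reduction in needs-thwarting behaviour is a likely false negative. The article does not say which of the nine scales count as thwarting.

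The response-format mismatch does not bias a comparison coded the same way in both periods. It is a wording error.

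**Conclusion.** The concern holds as a moderate one about a secondary outcome. With convenience selection, as few as one recording per NP per period and different patients in each period, a COUNSEL-CCE difference may partly reflect who was filmed. This rests on one assumption, that the patient influences the coded interaction, which fits an instrument that observes that interaction. Neither the direction nor the size of any bias can be derived from the documents.

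The two measurement notes are secondary. A null result on abandoning or awaiting, and to a lesser degree on clarifying, should not be read as evidence of no change. The response format contradicts itself and needs correcting.

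**What to change.** **Selection rule.** Replace the convenience choice with a rule applied identically in both periods. One example is a consecutive or randomly chosen consenting participant on pre-set filming days, at a comparable point in the patient's visits. In the experimental period, also fix the time after training. Simply taking the first patients who consent would be a poor choice there: it could capture only the earliest delivery, possibly before the booster session described under Training.

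**Recordings already made.** Inclusion began in September 2020, the article is the January 2021 version, and the first department crosses over in March 2021, so some control recordings may exist. A new rule would then cover one period better than the other. In that case, report how the control patients were chosen and compare the filmed patients' characteristics between periods, using the covariates already collected (gender, age, educational level, organ type, donor type).

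**Weak scales.** Add a sentence that a null result on abandoning, awaiting or clarifying will not be taken as absence of change.

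**Response format.** Reconcile the number of response points and the anchors with the manual before coding starts.

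**Cost.** Less freedom in scheduling the filming and a few changed sentences. No extra recordings or raters are needed. Selection by consent to be filmed remains.

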### Covariates

#### Patient-related

The following patient characteristics will be documented: *gender*, *age*, *educational level* (low, medium, high), *organ type* and *donor type (*deceased or living donation)*.* The question about donation will be completed by NP’s and not to by patients, due to the fact that patients are not always aware of the source of the organ.

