In an initial qualitative pilot study among 26 kidney transplant recipients, we assessed the acceptability and feasibility of this intervention. Patients valued the ZENN intervention and felt that this should be offered to all patients who have received a kidney transplant, particularly in the first year post-transplant [31]. Moreover, professionals reported the added value of the holistic approach in building a relationship of trust and promoting well-being [31]. We concluded that it was worthwhile to test the effectiveness of the ZENN intervention in future research.

In this article (version 1; January 2021), we describe the design of the ‘aanZET’-study. In this study, we will test the effectiveness of the ZENN intervention in promoting self-management skills among heart, liver, lung and kidney transplant recipients in comparison to standard care. The aims of the study are (1) to assess if the intervention has an effect on patients’ self-regulation and self-management skills, quality of life, medication adherence, coping and self-efficacy, controlling for socio-demographic and medical characteristics; (2) to assess if these changes are sustained over time after completion of the intervention; and (3) to test if the training and delivering the intervention has an effect on self-management support skills among NPs who provide outpatient care after transplantation.

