### Eligibility criteria

#### Patients

Eligible patients are heart, kidney, liver or lung transplant recipients who have received a transplant in one of the participating centres. The NP will ask patients to participate and hand out the written information on the study. Inclusion criteria are: over 18 years old, between two and thirteen months elapsed after transplantation, sufficient command of the Dutch language and the presence of a functioning graft. Exclusion criteria are cognitive limitations, participating in other lifestyle or self-management promoting programmes which could influence the outcome, and in case of kidney transplant recipients, an expected need for renal replacement therapy within 3 months of inclusion.

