### Data analysis

Data will be coded with a unique code per patient. The key of these codes will be safeguarded by the coordinating and the principal investigator with a password. No other persons will have access to the key. All data will be kept for 15 years, according to the Dutch Personal Data Protection law. Data will be stored using the data capture applications Gemstracker and Limesurvey. These systems are managed by the Department of Information Management of Erasmus MC and are secured with an individual password for the coordinating and principal investigator.

To assess if randomization has resulted in comparable groups, we will compare patients in the control and in the experimental period at baseline (T0) on characteristics as well as primary and secondary outcomes. Descriptive statistics will be presented as frequencies (%) for categorical variables. Continuous variables will be described as median and interquartile range for non-normally distributed variables and as mean and standard deviation for normally distributed data.

The primary analysis of the study is an initial univariate exploration of the effect of the intervention. Continuous outcomes at T1 between the patients in the control and experimental period will be compared and tested using the Mann-Whitney *U* test for non-normally distributed data and the independent-samples *t* test for normally distributed data. For the BAASIS, a 2 × 2 chi-squared test will be conducted (adherent yes/no × control/experimental group). In univariate analyses, the relationship between patient characteristics (such as age and gender) and medical characteristics (such as organ type and centre) and the outcomes will be assessed.

For the multivariate analyses, linear mixed models analysis will be conducted to account for repeated measures per patient, covariates organ and transplant centre and other significant covariates. All models will be estimated using intention-to-treat analysis incorporating all eligible patients from whom data was obtained. There are three measurement time points (T0, T1 and T2) to be included in these analyses. For missing data in predictor variables, we will use multiple imputation. A *p* value < 0.05 is considered statistically significant.

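### Time since transplantation is missing from the documented covariates, and covariates beyond organ and centre enter the model only if significant

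*Protocol article*

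**What the plan says.** Under Covariates, Patient-related, the protocol article states "The following patient characteristics will be documented" and names five: gender, age, educational level, organ type and donor type. The list is closed; it carries no wording such as 'for example'. Under Eligibility criteria, Patients, entry is allowed with "between two and thirteen months elapsed after transplantation", an 11-month spread.

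Under Data analysis, a first step is described with "In univariate analyses, the relationship between patient characteristics" and the outcomes; on the medical side it covers "medical characteristics (such as organ type and centre) and the outcomes will be assessed". The linear mixed model then accounts for repeated measures and for "covariates organ and transplant centre and other significant covariates". Organ and centre are therefore always in, and anything else has to earn its place by significance. The only threshold given is p < 0.05. The Introduction states the aim more broadly, as "controlling for socio-demographic and medical characteristics".

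Under Study design and randomization, departments are randomised to start dates. All seven begin in the control period, and the experimental patients are different people, recruited later.

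**The concern.** Randomisation fixes when a department switches, not which patient falls in which period. Within a department the contrast is between earlier and later recruits, so a patient characteristic that drifts with recruitment can be confounded with the intervention. Time since transplantation is an obvious candidate. When inclusion opens, recipients across the whole 2-13 month window are eligible at once, whereas later recruitment may draw more on newly eligible patients. Self-management skills may plausibly change during this part of recovery. If the characteristic both predicts the T1 score given baseline and differs between periods, part of that difference is credited to, or subtracted from, the intervention.

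The stated rule does not guard against this. Even if time since transplantation is screened, it enters only if its own test is significant. That test measures association with the outcome in the sample at hand and ignores imbalance between periods. It also leaves the final model dependent on the data.

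**Working it through.** **1. The plan's own figure.** Sample size: d = 0.38, two-sided 0.05, power 80%, patient-level ANCOVA with baseline. Without baseline adjustment, n = 2 × ((1.960 + 0.842)/0.38)² = 108.7, so 109 per group. With baseline-T1 correlation r, multiply by 1 − r². The article does not state r; r = 0.5 gives 108.7 × 0.75 = 81.5, so 82, as stated. The residual SD is then √0.75 = 0.866. This figure does not depend on time since transplantation and is not in question.

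**2. What the screen would keep.** Inputs: threshold 0.05 (Data analysis); n = 2 × 82 = 164 or the planned 200 (Sample size); the correlation ρ between covariate and outcome is assumed. The chance of selection is about 1 − Φ(1.96 − atanh(ρ) × √(n − 3)).

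| ρ | n = 164 | n = 200 |
|---|---|---|
| 0.1 | 25% | 29% |
| 0.2 | 73% | 81% |
| 0.3 | 98% | 99% |

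For ρ = 0.1 and n = 164: atanh(0.1) × √161 = 1.27, and 1 − Φ(0.69) = 0.25. This step needs no assumption about recruitment.

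**3. What omission could cost.** Assumptions, none of them in the documents: entry times uniform on 2-13 months, SD = 11/√12 = 3.18 months; 82 per group; partial correlation ρ of time since transplantation with the T1 score given baseline; mean imbalance of m months. Absolute bias = ρ × (m/3.18) × 0.866, in outcome SDs. The type I error is the two-sided rejection rate when the test statistic is shifted by bias/(0.866 × √(2/82)).

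| ρ | m = 1 | m = 2 | m = 3 | Share of 0.38 | Type I error |
|---|---|---|---|---|---|
| 0 | 0 | 0 | 0 | 0 | 5% |
| 0.1 | 0.03 | 0.05 | 0.08 | 7-22% | 5.5-9.3% |
| 0.2 | 0.05 | 0.11 | 0.16 | 14-43% | 6.9-22.7% |
| 0.3 | 0.08 | 0.16 | 0.25 | 22-65% | 9.3-44.2% |

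With no imbalance (m = 0) the bias is zero in every row. The sign depends on the direction of the imbalance and of the association, and the documents give neither.

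**4. The two steps together.** Take ρ = 0.2 and m = 2, and for illustration let the screening correlation equal the partial one. The bias if the covariate is omitted is 0.11 SD, and the screen would miss it in 1 − 0.81 = 19% to 1 − 0.73 = 27% of trials.

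**The case against.** The strongest reply has four parts.

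- **The article is condensed.** The examples in Data analysis are open-ended, the Introduction promises control for medical characteristics, and the transplant date must be known at entry. It would therefore go too far to say that time since transplantation will certainly stay unadjusted. What remains is the selection rule: it is stated, not left out, and it would apply to this variable too.

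- **A reader might infer that the factor is strongly prognostic and imbalanced by design.** The documents do not support this. The pilot remark in the Introduction about the first year after transplantation concerns how patients valued the intervention, not prognosis. A marked imbalance would follow if every eligible patient were captured promptly: an 11-month backlog plus L months of new recipients in the control period, against 20 − L months in the experimental period (September 2020 to May 2022 is about 20 months). For L = 6, 12 and 18 that gives 17 to 14, 23 to 8 and 29 to 2 months' worth of recipients; the three cases average 23 to 8, nearly 3:1. The plan is 100 per group, so prompt capture throughout fits poorly. If a larger pool is sampled slowly, the imbalance may be close to nil.

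- **Baseline absorbs part of the effect.** T0 is one of the repeated measures. If skills rose by the same amount every month, all patients would gain equally from T0 to T1 and the change from T0 would carry no bias. An ANCOVA with r near 0.5 would remove about half of a level difference. In an unadjusted T1 comparison, experimental patients nearer to transplantation would then score lower, which works against the intervention. Bias in its favour needs faster natural change soon after transplantation, which is possible but unquantified.

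- **Selection by p-value might be said to invalidate the confidence intervals.** That is not shown. Organ and centre stay in regardless, and the screen tests covariates against outcomes, not the treatment effect. The supported statement is that the rule makes the model data-dependent and can drop a real confounder.

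**Conclusion.** The point holds in this limited form. An entry characteristic with an 11-month spread is missing from the listed covariates, and the stated rule admits anything beyond organ and centre only on significance, in a design where patients are not individually randomised and controls always come first within a department. The weakness of the screen is firm, subject only to the assumed correlations. The bias from omitting time since transplantation cannot be fixed from the documents: zero if it is not prognostic given baseline or is balanced between periods, and up to about 0.25 SD (65% of the planned effect) at the far end of the assumed range. Its direction is open. This is a worthwhile improvement at almost no cost; it does not show that the trial will be biased.

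**What to change.** - Add time since transplantation at T0 to the patient characteristics in the Covariates section.
- In Data analysis, replace "and other significant covariates" with a set entered regardless of significance: organ and centre as now (or department, which carries both), time since transplantation, age, gender, educational level and donor type, with the T0 score in the model.
- Keep the univariate associations as description only, and say that they do not select covariates.

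The change acts on the mixed model. An unadjusted comparison at T1 is untouched by it and should not be relied on for confounding control.

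Cost: no new data collection, because the transplant date is needed to check eligibility. With linear age and time terms, the additions beyond organ and centre take 1 + 1 + 1 + 2 + 1 = 6 degrees of freedom (age, gender, time since transplantation, three-level education, donor type), which is small with 164 to 200 patients.
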